### 2.5. Recruitment

Participants will be prospectively included and compared with historical controls from the same sites. Participants meeting all the inclusion and not any of the exclusion criteria will be offered to start on the HR^35^ZE arm. After 8 weeks, participants will be managed according to the national TB guidelines.

The selected retrospective participants will provide a comparison for the primary safety outcome, and to the secondary efficacy outcome of culture conversion at 8 weeks using MGIT media. 

We adhered to all Pockock’s principles for historical controls except for the use of information from participants that were previously randomized in clinical trials [23]. To avoid the selection bias that may arise because of this limitation, we aim to include all adult patients fulfilling the inclusion criteria treated with HR^10^ZE in the participating sites between January 2017 and December 2019 (to avoid the influence of the 2020–2021 SARS-CoV-2 pandemic in TB diagnoses and follow-up). Thus, the records of all patients from that period with pulmonary and extrapulmonary rifampicin susceptible tuberculosis will be reviewed. We will capture the severe or grade 3 adverse events and week 8 microbiological status from those who are ≥60 years, or ≥18 years and have a diagnosis of diabetes, malnutrition, HIV, HBV or HCV coinfection, other stable chronic liver diseases, or TB meningitis, and have no pharmacological immunosuppression. We intend to control the retrospective cohort to match the prospective one for age, sex, cavitation in lung TB, and severity in TB meningitis. In case not enough matched controls are not found, we will extend the search with patients until the calculated sample size in the control arm is achieved. The historical cohort will include participants from only Spain, Portugal, and Paraguay and not likely from the Netherlands, as optimized doses of rifampicin have been used in both Dutch sites for more than a decade in the same participant subgroups as included in our study.

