### 2.8. Assessment of Study Outcomes, Analysis Groups, and Duration of Follow-Up

The primary safety hypothesis is that the incidence of adverse events in the high dose rifampicin (35 mg/kg) supplemented with isoniazid, pyrazinamide, and ethambutol [HR^35^ZE] during the first 8 weeks of treatment will not exceed that of controls on a standard HRZE regimen (rifampicin 10 mg/kg) [HR^10^ZE]. The HR^35^ZE regimen will be considered unsafe if in a non-inferiority analysis, the upper limit of the 95% confidence interval of the difference of proportions in grade ≥ 3 AE (according to CTCAE scale version 5) between the experimental and the historical control arm exceeds 8%. The most common adverse events related to therapy with higher rifampicin doses were vomiting, headache, hyperuricemia, pain in the extremities, and pruritus. No significant differences according to rifampicin dose (from 10 to 35 mg/kg) were found in a recent systematic review and in a retrospective study collecting the real-life experience from a Dutch center [24,25].

To assess the AE and ensure a homogeneous evaluation of their grade, severity, expectedness, and treatment relatedness, we will administer a standardized training for the investigators from all different sites. In addition, both for the prospective and the retrospective cohorts, grade 3 or higher adverse events and SAE will be reviewed by the trial’s Steering Committee for relatedness classification. When no consensus is reached, the Data and Safety Monitoring Board formed by experts independent from the trial will make the final decision.

Tolerability will be measured as any adverse event (grade 1 to 4), treatment dropout rate, and any dose reduction. For efficacy outcome, the hypothesis is that in DS-TB participants (pulmonary disease), the proportion of participants experiencing successful treatment outcomes (culture and smear negative) at the end of the intensive phase of treatment on HR^35^ZE will be non-inferior to that of controls on HR^10^ZE. The HR^35^ZE regimen will be considered ineffective if the lower limit of the 95% CI of the proportion of participants with a negative sputum culture (sputum sterilization), or unable to produce sputum if they have a previous negative culture at week 8, is more than 10% lower than that of historical controls treated with HR^10^ZE. Other exploratory outcomes will be reported descriptively. 

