### 2.11. Secondary Objectives

Secondary objectives can be grouped into 4 categories. The analyses will be descriptive as these data will not be available from most of the historical HR^10^ZE controls.

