#### 2.11.1. Microbiological Evaluation

We will collect sputum samples from the experimental treatment pulmonary TB participants at week 1, 2, 4, 6, and 8, and compare the baseline bacterial load with the bacterial load at each of these time points as estimated by the time to positivity in days, as compared to that at baseline [9]. Time to positivity (TTP) is a good correlate of bacterial load and this information is readily available from the MGIT system. In addition, we should be able to estimate CFU count using a formula previously published [26]. In addition, we will compare the changes in TTP with a baseline and follow-up breath signal of the AeoNose™ device, an electronic nose that analyzes volatile organic compounds (VOC) in exhaled air. Pilot studies show that the VOC signal decreases during treatment; hence, it has potential as a biomarker to estimate bacterial load [27].

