Therefore, the population included in this study belong to the other risk factors groups for failure and relapse that have been under-represented in previous clinical trials [4,22]. As a phase 2 study, the main aim of this clinical trial is to evaluate safety of rifampicin defined as the rate of participants suffering grade 3 or higher adverse events or severely adverse events. This information will be likely available from historical controls although it was not systematically collected. Grade 1–2 adverse events, which are considered tolerability problems, are not typically reported in clinical records, or the information about them is not complete, thus making it difficult to make comparisons. To address this, we have developed adverse events monitoring and management guidelines, which will be harmonized at all centers for the prospective part. Extensive training will be provided to the investigators at each site. 

It is important to acknowledge the main limitations related to this trial design. Because of the limited recruitment capacity within our consortium and budgetary constraints, we decided to use historical controls (rifampicin 10 mg/kg along with the same TB regimen) and assign all prospectively recruited participants to the 35 mg/kg dose. This results in a non-randomized design as all participants will be assigned to the experimental arm and compared with historical controls. Hence, another limitation is that information about tolerability is often incomplete or not reported in clinical records, and the endpoints in the different sub-studies are not performed in daily clinical practice. For similar reasons, the sample size is too small for a formal subgroup analysis. The results will inform a larger phase 3 trial with power calculations for relevant subgroups.

Having one PK sampling at week 4 will allow us to show the percentage of participants reaching the target exposure (AUC/MIC) when in a steady state after rifampicin induction of its own metabolism. In contrast, this approach will not provide information about exposure during the first week of treatment, when most of the bacterial killing occurs. Nevertheless, this knowledge will aid our understanding if optimized rifampicin dosing is more likely to meet target rifampicin exposure. 

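### Section 2.8 credits week-8 sputum non-producers only if an earlier culture was negative, a condition HR35ZE participants can meet and most historical controls could not; section 2.10 classifies the same patients differently

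*Protocol article*

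**What the plan says.** Section 2.8 sets the efficacy decision for pulmonary TB. Success is a negative sputum culture "or unable to produce sputum if they have a previous negative culture at week 8". HR35ZE is called ineffective if the lower 95% confidence limit of that proportion "is more than 10% lower than that of historical controls treated with HR^10^ZE". This is a formal comparison with a 10-point margin.

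Section 2.5 uses the controls for the safety comparison and extends their use "to the secondary efficacy outcome of culture conversion at 8 weeks using MGIT media". On data capture it says: "We will capture the severe or grade 3 adverse events and week 8 microbiological status from those" who belong to the listed risk groups. No earlier culture is named.

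Section 2.11.1 gives the prospective schedule: "We will collect sputum samples from the experimental treatment pulmonary TB participants at week 1, 2, 4, 6, and 8". Section 2.11, which introduces that subsection, says that "these data will not be available from most of the historical HR^10^ZE controls". The Discussion adds that "the endpoints in the different sub-studies are not performed in daily clinical practice".

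Section 2.10 defines the unfavorable efficacy outcome as a positive week-8 culture and does not mention patients who cannot produce sputum.

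**The concern.** Whether a non-producer counts as a success in section 2.8 depends on a second piece of information, an earlier negative culture. The study creates that information on schedule in one cohort, and the article does not plan to collect it in the other. Two patients with the same course (sputum dried up by week 8, no positive culture) can then be classified differently because one was sampled serially and the other was not.

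Such a difference in ascertainment enters the estimated difference directly and has nothing to do with the drug. In a non-inferiority comparison, a shift towards HR35ZE raises the chance of a false conclusion of non-inferiority. A shift the other way raises the chance of calling an adequate regimen ineffective. Unlike the lack of randomisation, this source of bias can be avoided.

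**Working it through.** **1. The passages side by side**

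| | HR35ZE | Historical HR10ZE |
|---|---|---|
| Planned cultures on treatment before week 8 | weeks 1, 2, 4, 6 (2.11.1) | none listed (2.5) |
| Week-8 result | yes | yes |
| Non-producer under 2.8 | success if an earlier culture was negative | success if an earlier culture was negative, but none is planned to be abstracted |
| Non-producer under 2.10 | not unfavorable | not unfavorable |

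The asymmetry exists under section 2.8 and disappears under section 2.10. Section 2.8 does not say whether a non-producer who fails the condition is a non-success or is left out.

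**2. Illustration of size**

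The article states no efficacy sample size and no rate of non-production, so there is no figure of its own to reproduce. All inputs except the margin are assumptions:
- u, share unable to produce sputum at week 8, equal in both cohorts: 10%, 20%, 30%
- qE, share of HR35ZE non-producers with an earlier negative culture: 50%
- qC, the same share in controls: 0
- p, success among producers, equal in both cohorts (no drug effect): 80%
- margin: 10 points (section 2.8)

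Three ways of handling unqualified non-producers:
- A, non-success in both cohorts: HR35ZE = (1−u)p + u·qE; control = (1−u)p + u·qC; shift = u(qE − qC)
- B, dropped in both: HR35ZE = [(1−u)p + u·qE] / [(1−u) + u·qE]; control = p
- C, non-success in HR35ZE, dropped among controls: HR35ZE as in A; control = p

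| u | A | B | C |
|---|---|---|---|
| 10% | 77 vs 72: +5 | 77/95 = 81.1 vs 80: +1.1 | 77 vs 80: −3 |
| 20% | 74 vs 64: +10 | 74/90 = 82.2 vs 80: +2.2 | 74 vs 80: −6 |
| 30% | 71 vs 56: +15 | 71/85 = 83.5 vs 80: +3.5 | 71 vs 80: −9 |

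Entries are percentages, HR35ZE against control, followed by the shift in points; plus favours HR35ZE. If some controls do have an earlier negative culture on file, say qC = 30%, the shift under A falls to u × 0.20, which is 2, 4 and 6 points.

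**3. Effect on the decision under A**

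Assume 100 pulmonary patients per cohort, 80% in controls, and 70% in HR35ZE before any shift, so that the true deficit equals the margin. With no shift, the chance of declaring non-inferiority is 2.5%. With a 5-point shift, SE = √(0.80×0.20/100 + 0.75×0.25/100) = 0.0590, and Φ(0.05/0.0590 − 1.96) is about 13%.

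**4. Check of the remedy**

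With one rule for both cohorts and equal u, the shift is zero. Counting non-producers as successes gives (1−u)p + u in each cohort; treating them as not assessable gives p in each. If u differs between cohorts, the two rules can give different answers, which is why both should be reported.

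**The case against.** Section 2.5 does not say that only the week-8 result is captured. A week-8 status could be assigned from the whole chart, including an earlier negative culture, and the abstraction form belongs to a full protocol that is not shown. Section 2.11 introduces several sub-studies together and speaks of most controls, not all. This much stands: it cannot be said that no control could ever meet the condition, and setting qC to 0 is an assumption. It does not remove the problem. The article makes success depend on an earlier culture, schedules such cultures for one cohort, and names no counterpart for the other.

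A reader might infer that the rule necessarily favours HR35ZE and can consume the whole margin. The documents do not support that. It needs every unqualified control non-producer to count as a non-success, which no section states. Under C the sign reverses.

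A reader might also take the wording literally, as asking for a week-8 culture from someone with no week-8 sputum, so that it applies to nobody. It is better read as a slip of word order, with the time point closing the whole clause.

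Finally, efficacy is secondary, and section 2.15 and the Discussion concede that historical controls invite bias. That limits the consequence but does not justify a definition that adds to it.

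**Conclusion.** The point holds as a defect in the endpoint definition. As written, section 2.8 lets HR35ZE non-producers qualify for success through scheduled cultures that most controls would lack, and section 2.10 classifies the same patients by a different rule.

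Neither the size nor the direction of the bias can be fixed from the article. On the assumptions in the working it ranges from 15 points towards HR35ZE to 9 points against it, and it is only about 1 to 3.5 points if unqualified non-producers are dropped in both cohorts. The range rests on assumed non-production of 10–30%, half of HR35ZE non-producers with an earlier negative culture, no such controls, and 80% success among producers. Set against a 10-point margin, this is enough to require one stated rule before control records are abstracted. It should be corrected, but it does not touch the primary safety outcome.

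**What to change.** - For the 10-point comparison, use one definition in sections 2.8 and 2.10 that classifies week-8 non-producers identically in both cohorts and does not use interim cultures.
- Name either success in both or not assessable in both as the main rule, and report the other as a sensitivity analysis. Which of the two leads is open to argument; that it is the same in both cohorts is not.
- Record in both cohorts the reason for a missing week-8 sputum, so that inability to produce is separated from a sample that was never requested.
- Keep the earlier-culture condition for the descriptive HR35ZE analysis only.
- Reword the clause in section 2.8 so that week 8 refers to the assessment and not to the earlier culture.

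The cost is a small text change in two sections, one more chart field, and possibly slightly fewer assessable participants.

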### 2.2. Objectives and Endpoints

The study primary objective is to evaluate the safety of high-dose rifampicin (35 mg/kg/d) as part of a standard first line regimen using standard doses of isoniazid (5 mg/kg), pyrazinamide (25 mg/kg), and ethambutol (15–25 mg/kg) for 8 weeks in adult subjects with pulmonary or extrapulmonary DS-TB belonging to difficult to treat subgroups. The secondary objectives are to evaluate the tolerability, efficacy, bactericidal activity, pharmacokinetic/pharmacodynamics, and cost effectiveness of high dose rifampicin, among others. 

The primary safety endpoint is the proportion of participants and historical controls with one or more grade 3 or higher adverse events (AE) according to the CTCAE v5 or SAE at 8-weeks after treatment with high-dose rifampicin onset. Table 2 below describes in detail the analysis population and primary safety outcomes. The secondary tolerability endpoint includes the proportion of participants with any AE. The secondary efficacy endpoint includes the proportion of participants and historical controls who have sputum culture conversion at 8 weeks after treatment onset or a proportion of participants with clinical improvement according to the treating physician (if follow-up images are available for extra-pulmonary TB) but without a follow up sample at 8 weeks after treatment onset.

Most TB phase 2 trials complete their intervention at week 8 or earlier and then participant care is transferred to a public institution within the National TB programs, so the information about end of treatment and post-treatment outcomes is scarce [10,17,18]. In the RIAlta trial, after the intervention and the primary safety objective evaluation, an extended follow-up period will be offered to participants, in line with the phase 2b/c design suggested by Phillips et al. [19]. This will provide information about end-of-treatment outcomes and relapse incidence in the prospective group.

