### 2.10. Main Outcomes Analysis

The primary safety outcome will be analyzed as the proportion of participants in the HR^35^ZE and historical HR^10^ZE groups that received at least one dose of treatment with an unfavorable outcome after 8 weeks of experimental treatment start. According to the clinical and laboratory information, participants will be classified as having an unfavorable outcome if they suffered one or more grade ≥ 3 AE or SAE that are possibly, probably, or definitely related to rifampicin OR they did not complete their treatment because of other reasons OR were lost-to follow-up. High doses of rifampicin will be considered non-inferior to standard doses if the upper boundary of the 95% CI of the proportion of participants with an unfavorable outcome is less than 8% that of the point estimate in the historical standard dose group.

Efficacy will be assessed as the proportion of participants with pulmonary TB in the HR^35^ZE and the historical HR^10^ZE groups that have sputum culture conversion in liquid media at week 8. The unfavorable efficacy outcome will be defined as having a positive sputum culture at week 8.

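### The week-8 efficacy outcome behind the 10-point non-inferiority rule is defined inconsistently, and the section 2.8 no-sputum rule depends on earlier cultures scheduled only for HR35ZE

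*Protocol article*

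**What the plan says.** All references are to the protocol article.

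- **Section 2.8, hypothesis.** In pulmonary disease, the comparison is of "successful treatment outcomes (culture and smear negative) at the end of the intensive phase of treatment".
- **Section 2.8, decision rule.** Success is a negative sputum culture, or being "unable to produce sputum if they have a previous negative culture at week 8". Smear is no longer mentioned. The 10-point margin against the historical controls is attached to this version.
- **Section 2.10.** Efficacy is the proportion of pulmonary patients "that have sputum culture conversion in liquid media at week 8". On the other side, "The unfavorable efficacy outcome will be defined as having a positive sputum culture at week 8".
- **Section 2.2.** The efficacy endpoint is sputum culture conversion at 8 weeks, or "clinical improvement according to the treating physician (if follow-up images are available for extra-pulmonary TB) but without a follow up sample".

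On data collection the cohorts differ. Section 2.11.1: "We will collect sputum samples from the experimental treatment pulmonary TB participants at week 1, 2, 4, 6, and 8". For controls, section 2.5: "We will capture the severe or grade 3 adverse events and week 8 microbiological status". Section 2.11 adds that the data for its secondary objectives, which include the serial sputa, will be lacking for most controls.

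**The concern.** A formal non-inferiority rule needs one outcome that puts each patient in one category. Here a patient who is culture negative but smear positive, who has no sputum, or who dies before week 8 is classified according to the section the analyst follows. The controls were treated in 2017–2019 and the trial is open-label, so leaving several definitions open also leaves room to choose among them once results are known.

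One of the definitions also treats the cohorts unequally. The no-sputum route to success in 2.8 requires a documented earlier negative culture. The plan schedules such cultures in HR35ZE and does not plan to capture them in controls. Patients with the same true status could then be successes in one cohort and not in the other.

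**Working it through.** **Step 1. The definitions side by side**

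| Patient | 2.8 hypothesis | 2.8 decision rule | 2.10 |
|---|---|---|---|
| Culture negative, smear positive | not a success | success | converted |
| No sputum, earlier negative culture | not shown to be a success | success | not unfavorable, not clearly converted |
| No sputum, no earlier negative | not shown to be a success | not a success; failure or excluded is not stated | not unfavorable, not clearly converted |
| Death before week 8 | not a success | not addressed | not unfavorable, not converted |

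The 2.8 decision rule is also unclear in itself. Read literally, it asks for a week-8 culture from someone who cannot produce sputum. The workable reading is an earlier negative culture, and it is used below.

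**Step 2. Inputs for the size**

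The article gives no expected conversion rate, sample size or power for efficacy, so there is no stated figure to reproduce. Only the 10-point margin (2.8) comes from the document. The rest are assumptions, with no true difference between cohorts:

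- s, share with no week-8 sputum, equal in both cohorts: 20% (also 10%)
- hE, hC, share of these with an earlier negative culture: 70–80% in HR35ZE, 20–30% in controls
- c, culture-negative share among sputum producers, equal in both cohorts: 75–85%

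**Step 3. 2.8 rule, no earlier negative counted as failure**

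Success = (1 − s)·c + s·h, so the artificial difference is s·(hE − hC).

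- 0.20 × (0.8 − 0.2) = 0.12
- 0.20 × (0.7 − 0.3) = 0.08
- with s = 10%: 0.10 × 0.6 = 0.06 and 0.10 × 0.4 = 0.04

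**Step 4. 2.8 rule, no earlier negative excluded**

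Success = [(1 − s)·c + s·h] / [(1 − s) + s·h], with s = 20%.

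- c = 75%, 0.8 vs 0.2: 0.76/0.96 = 79.2% vs 0.64/0.84 = 76.2%, difference 3.0 points
- c = 75%, 0.7 vs 0.3: 0.74/0.94 = 78.7% vs 0.66/0.86 = 76.7%, difference 2.0 points
- c = 85%, 0.8 vs 0.2: 0.84/0.96 = 87.5% vs 0.72/0.84 = 85.7%, difference 1.8 points
- c = 85%, 0.7 vs 0.3: 0.82/0.94 = 87.2% vs 0.74/0.86 = 86.0%, difference 1.2 points

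**Step 5. 2.10 rule, only a positive culture unfavorable**

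Favorable = 1 − (1 − s)·(1 − c). Earlier cultures do not enter. With s = 20% it is 80% (c = 75%) or 88% (c = 85%) in both cohorts, a difference of 0.

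**Step 6. Check on the remedy when missingness is unequal**

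Assume 10% of HR35ZE and 30% of controls have no week-8 result, with 80% conversion in both.

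- No result counted as not converted: 0.90 × 0.80 = 72% vs 0.70 × 0.80 = 56%, 16 points in favour of HR35ZE
- No result counted as negative: 1 − 0.90 × 0.20 = 82% vs 1 − 0.70 × 0.20 = 86%, 4 points against HR35ZE

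Neither convention is neutral by itself.

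**The case against.** The strongest reply is that the difference lies in wording and the bias is conditional. Much of this stands.

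- **The bias depends on the section followed.** The earlier-negative credit exists only under 2.8. The fact that deaths and losses are not unfavorable arises only under 2.10, which treats both cohorts alike. The two effects cannot be added, and the text does not fix a direction for the second.
- **The asymmetry is partly inferred.** Section 2.5 does not say that routine earlier cultures in control records are absent or will be ignored. The remark in 2.11 concerns the sub-studies and says most controls, not all. Any interim cultures on record would shrink the effect.
- **The clinical-improvement route is not clearly a rival definition.** A reader might infer from 2.2 that an open-label physician judgement enters the non-inferiority test. The wording ties that route to extrapulmonary TB with images, while 2.8 and 2.10 compare pulmonary patients only.
- **The population is largely supplied.** A reader might infer from Table 2 that extrapulmonary cases enter the efficacy comparison, because its intention-to-treat row takes everyone enrolled. But 2.10 restricts efficacy to pulmonary TB, and Table 2 already has a microbiological intention-to-treat population with culture-confirmed disease.
- **Detail may sit elsewhere.** Handling of deaths and missing samples is commonly left to the full protocol or SAP.

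The last argument does not dispose of the point. The issue is that the rules the article does state conflict, and that one of them rests on data planned for one cohort only.

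**Conclusion.** The point holds in a limited form. Sections 2.8 and 2.10 give three non-equivalent outcomes for one 10-point non-inferiority comparison, and the 2.8 decision rule can favour HR35ZE.

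A reader might go further and conclude that the efficacy comparison is biased towards HR35ZE by about the width of the margin. The documents do not support that. On the assumptions in the working with 20% lacking week-8 sputum, the artefact is 8–12 points only if patients with no sputum and no earlier negative count as failures, which the article does not say. It is about 1–3 points if they are excluded, and 0 under 2.10. That the answer ranges from nothing to about the whole margin according to the section followed is itself the defect.

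Efficacy is a secondary endpoint. The primary safety conclusion is unaffected.

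**What to change.** 1. State one definition in both 2.8 and 2.10: the week-8 liquid (MGIT) culture result in culture-confirmed pulmonary TB, using Table 2's microbiological intention-to-treat population restricted to pulmonary cases. Section 2.5 already names MGIT culture at 8 weeks for the control comparison.
2. Remove the dependence on interim cultures, and say whether smear plays any part.
3. Classify no sputum, death and loss to follow-up by the same written rule in both cohorts.
4. Report the number with no week-8 result by cohort, and the comparison under both extremes: no result counted as not converted, and no sputum counted as negative. The first alone may favour HR35ZE if routine control records lack more week-8 cultures.
5. State in 2.2 that physician-judged improvement in extrapulmonary TB is a separate descriptive measure outside the non-inferiority comparison.

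The cost is wording and a little extra analysis. The efficacy conclusion may become less clear-cut if the two extremes disagree.
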